#### Statistical analyses

To test the effectiveness of the digital app, a case-control study will be performed (see Fig. 6 in Appendix). Cases are newly recruited individuals that fulfil the inclusion criteria outlined in Table 6. Comparators/controls are the participants in one of the two intervention arms of the previously conducted RCT study in Phase 2 (i.e. patients; historical control groups; No-Treatment CG _analysis_: *N* = 176; No-Treatment CG _recruited_: *N* = 212; Previously Treated/Active CG _analysis_: *N* = 176 (called IG1 in Fig. 6 in Appendix); Previously Treated/Active CG _recruited_: *N* = 212, see in section Phase 2). *N* = 176 participants need to be analyzed for the intervention group (IG2 _analysis_). Assuming a drop-out of 20%, *N* = 212 participants have to be recruited for the intervention group (IG2 _recruited_) in Phase 3 (see Fig. 6 in Appendix). The intervention will also be provided to the professionals in the clinic. Adoption and acceptance of the intervention will be evaluated in all groups by means of observational data and self-report. Target criteria are specified in Tables 1 and 2.

At the end of Phase 3, the results from all three phases will be disseminated using a white paper with recommendations for practice. Further plans to communicate trial results to participants, healthcare professionals, the public, and other relevant groups via publication, presentations and press releases will be developed using a participatory approach, with the restriction that anonymity is ensured at all times.

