This will be scientifically evaluated using a three-phase study, in which phases are built sequentially on each other and described in detail in the method section: Phase 1, *implementation phase* (including needs assessment, retrospective cohort study of pAEs) *and pre-experimental study* with a group and pre−/post-test testing the effect of a training for professionals; Phase 2, *quasi-experimental efficacy study* with a randomized controlled trial study design (RCT) testing the effect of a training addressing patients and their social support providers; Phase 3, implementation of the app, aimed at staff, patients, and their social support providers, which will test the effect in *a case-control study*. Efficacy indicators are outlined in Table 1.

The *hypotheses* are the following: for Phase 1, it is expected that as a result of the training (1.) the communication competences of healthcare providers will measurably improve. As a result, (2.) healthcare providers will be more satisfied (3.) and the number and severity of pAEs should be significantly reduced for short and medium term (i.e. over the period of the intervention study and beyond). In Phase 2, it is expected that patients and their social support providers in the intervention group will develop significantly (4.) higher competences in communication with staff as well as (5.) higher satisfaction after the intervention compared to patients and their social support providers in the control group. It is also expected that (6.) the number and severity of pAEs in the intervention group will be significantly reduced compared to the number and severity of pAEs in the control group. For Phase 3, we hypothesize that the intervention group using the app compared to the intervention group without the app will show (7.) higher patient and healthcare provider communication competences and (8.) satisfaction as well as (9.) a significant reduction in the number and severity of pAEs. The effects of the training on communication competences may be (10.) mediated by training-related and personal outcomes and moderated by organizational factors (11.). All interventions in all phases will improve organizational outcomes if communication competences are improved successfully. Thus, the hypotheses will be tested in this project.

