#### Procedure, sample and data collection

Patients will be recruited via doctors and midwives in the hospitals; recruitment of staff and collection of informed consent of both patients and staff will be conducted by the on-site project managers. Quality management departments will be involved to ensure adequate participant enrollment to reach the target sample size. The target criteria of the patient sample will be evaluated statistically and clinically as in Phase 1 and 2 (see Table 2). Group differences will be tested with linear and general mixed models and with *superiority trial tests* that investigate whether the intervention is helping more than the standard care in Phase 2.

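### Phase 3 compares app users with an earlier cohort, so its superiority tests cannot separate the effect of the app from calendar period

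*Protocol article*

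**What the plan says.** All references are to the protocol article.

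- **Aim.** Phase 3, Statistical analyses: "To test the effectiveness of the digital app, a case-control study will be performed".
- **App group.** Same section: "Cases are newly recruited individuals that fulfil the inclusion criteria outlined in Table 6". They are recruited after Phase 2 and are not randomised.
- **Comparator.** Same section: "participants in one of the two intervention arms of the previously conducted RCT study in Phase 2". The text labels these as historical controls and then lists both the untreated and the trained Phase 2 groups.
- **Hypotheses 7 to 9.** Research questions and hypotheses contrasts "the intervention group using the app compared to the intervention group without the app", which points to the trained Phase 2 cohort. The Phase 3 procedure section instead names Phase 2 standard care as the comparator for its superiority tests.
- **Analysis.** Phase 3, Procedure, sample and data collection: "Group differences will be tested with linear and general mixed models", following Phases 1 and 2. Phase 1 specifies T1 values as covariates and clinic as a fixed effect. Phase 2 adds ANCOVAs with factors such as education, anxiety and immigration status. No term for period is stated.
- **Who gets the app.** Phase 3, Statistical analyses: "The intervention will also be provided to the professionals in the clinic". The Abstract, the research questions and the Functions of the app section all describe an app for staff, patients and support providers together.
- **Use of the result.** Results of all three phases feed a closing white paper that makes recommendations for practice.

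**The concern.** The hypotheses and the superiority tests are worded as claims about what the app does. The comparison made is between two cohorts from different periods. Its null hypothesis is that the Phase 2 and Phase 3 cohorts do not differ, which is not the same as no app effect. Anything that changes between the phases can make that null false.

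The protocol itself gives reasons to expect change:

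- It predicts that the Phase 1 staff training will lower preventable adverse events during the study and afterwards.
- Stages D and E are repeated with staff, patients and supporters before the app is tested.
- Phase 2 recruits through doctors, nurses and midwives; Phase 3 names only doctors and midwives.
- If the Phase 2 trainers continue, they enter Phase 3 with more experience.

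The design label adds to the difficulty. A case-control study selects people by outcome; here groups are defined by exposure and period. At stake is whether a significant Phase 3 result may be reported as a causal effect of the app.

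**Working it through.** **Inputs.** From the document: d = 0.3, alpha 0.05, power 80% (Phase 2, Procedure), and 176 analysed in the app group and in each historical group (Phase 3, Statistical analyses). Assumed: period shifts of 0.10, 0.15 and 0.20 SD on a continuous score, T1–T2 correlation r = 0.5, independent patients, two-sided test. The document gives no drift figure and no correlation.

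**1. The plan's own figure.** A two-sided two-sample calculation for d = 0.3 gives 175 per group (normal) or 175.4, hence 176 (t-test). Power with 176 is 80.4% by the normal formula. A one-sided test would need 138. The stated 176 reproduces as two-sided.

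**2. Shift arising after T1, unadjusted.** SE = sqrt(2/176) = 0.1066 SD, so a difference of 1.96 × 0.1066 = 0.209 SD is significant. With the app effect set to zero, P(reject) = P(|Z + shift/SE| > 1.96).

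| Assumed shift (SD) | Significant | Of which in favour of the app |
|---|---|---|
| 0 | 5.0% | 2.5% |
| 0.10 | 15.5% | 15.3% |
| 0.15 | 29.1% | 29.0% |
| 0.20 | 46.7% | 46.7% |

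**3. Shift equally present at T1 and T2, with T1 adjustment.** ANCOVA with equal variances removes r × shift, leaving (1 − 0.5) × shift. SE = 0.1066 × sqrt(1 − 0.25) = 0.0923.

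| Assumed shift (SD) | Shift left (SD) | Significant |
|---|---|---|
| 0.10 | 0.050 | 8.4% |
| 0.15 | 0.075 | 12.8% |
| 0.20 | 0.100 | 19.1% |

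T1 adjustment therefore removes only part of a drift that is already visible at T1. It removes none of a change in care, staff behaviour or event recording that comes after T1.

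**4. Sample size and direction.** More patients do not help: at a shift of 0.10 SD, a significant result in favour of the app has probability 26.3% with 352 per group, against 15.3% with 176. Drift can also hide an effect: with a true effect of 0.30 SD and drift of −0.10 SD, power falls from 80.4% to 46.7%.

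**5. What a drift adjustment could deliver.** Suppose a linear time slope is estimated in the trained Phase 2 arm alone (n = 176), with even enrolment over a phase of length L. The slope has variance 12/(176 L²). Carrying it from the midpoint of Phase 2 to the midpoint of an adjacent Phase 3 of equal length multiplies it by L. The adjusted difference then has SE = sqrt(2/176 + 12/176) = sqrt(14/176) = 0.282 SD, against 0.107 unadjusted. Power at d = 0.3 would be P(Z > 1.96 − 0.3/0.282) = about 18.5%. A linear slope within Phase 2 also cannot detect a step change between the phases.

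**The case against.** **The app is meant for staff as well.** This stands. The research questions describe the "implementation of the app, aimed at staff, patients, and their social support providers, which will test the effect in" Phase 3 study, hypothesis 7 covers provider competences, and the Functions of the app section states the same three-party aim. A reader might infer from the sentence about professionals that staff use contaminates the comparison. The documents do not support that: staff use is part of the package. It becomes a misattribution only if the result is read as the effect of patients' own app use, which the wording of hypotheses 7 to 9 and the patient-level sizing may invite. Calendar drift matters under either reading.

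**The historical controls are declared.** True, and any such design has this limitation. But the label is disclosed without its consequence: effectiveness and superiority wording is kept, and the design is called case-control.

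**Baseline adjustment deals with drift.** In part. It would be too strong to say that the stated covariates do nothing, since case-mix or recruitment changes that show at T1 are partly removed (working, step 3). They still cannot separate period from app.

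**No drift is documented.** Correct. The shifts are assumptions, so the percentages show sensitivity and do not predict an error rate.

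**The white paper draws on all three phases.** Also correct. It includes the randomised Phase 2, so its recommendations do not rest on this contrast alone.

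**Conclusion.** The concern holds in a bounded form. Phase 3 is a non-randomised comparison of a later cohort with historical controls, and the planned analysis cannot attribute a difference to the app rather than to period. If the app had no effect, an assumed shift of one third of the planned effect (0.10 SD) would give about 15% significant results unadjusted if it arises after T1, and about 8% if it is equally present at T1 and T2 and T1 is adjusted for with r = 0.5. For 0.20 SD the figures are about 47% and 19%.

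A reader might go further and conclude that Phase 3 is uninformative or that drift has been shown. Neither follows. The comparison can still describe how the two cohorts differ; what it cannot support is a causal superiority claim for the app. Phase 3 can proceed with its conclusion reworded.

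**What to change.** 1. **Restate the target** in Research questions and hypotheses (7 to 9) and in the Phase 3 procedure and statistical analyses sections: the difference between the cohort treated after the app was introduced for patients, supporters and staff together and the earlier Phase 2 trained cohort. Use that comparator consistently. Against the untreated group, the contrast would also include the face-to-face training that app users have completed.
2. **Rename the design** as a historically controlled cohort comparison.
3. **State the limits:** period effects and the separate contribution of patients' own app use are not identified. The white paper should therefore make no causal superiority claim for the app from this contrast.
4. **Report the calendar-time trend within Phase 2,** with its interval, as a descriptive sensitivity analysis. Admission days are known because allocation is per site and day. It should not be a condition for the claim. Note that it is imprecise (SE of the drift-adjusted difference about 0.28 SD if estimated in one arm, assuming adjacent phases of equal length) and blind to a step change between phases.

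**Cost.** Changes of wording, one extra and imprecise analysis, and a narrower claim. No additional patients are needed.

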## Discussion

This project investigates interpersonal communication based on communication competences and the Health Action Process Approach (HAPA) to better understand where and how problems may occur and how to overcome these problems with interventions in everyday clinical life. Currently, there is no study that has done so in everyday clinical practice and has demonstrated the effectiveness of corresponding interventions based on the two theories as theoretical backdrop for designing the intervention.

The overall aim of the project is to support communication based on the communication competences model and the HAPA, and to overcome difficulties in everyday hospital life. The project is characterized by three innovative aspects. The first innovative aspect is the theoretical background and its application to maternity clinics. The *communication competences model* has been specifically designed to address communication in the healthcare context, whereas the *HAPA model* has been shown to bridge the gap between intention and behavior [25]. The combination of both HAPA and communication competences will aid in the design of an intervention specifically tailored to the healthcare context, which increases its potential effectiveness.

The second innovation of this project lies in its *digital focus, and thus, a focus on innovation policy*. The question is, to what extent can digital support of interpersonal communication actually support effective communication and which evidence-based recommendations can be given? Although there is some evidence, which we have reviewed in the beginning of this paper, this new project has a clear innovative potential to set the stage for future research in public health and prevention.

The third innovative aspect of this project lies in its systematic empirical investigation of *including professionals, patients and their social support providers* as active partners for patient safety. This adds to the value of this project by assessing dyadic data and is currently also regarded by the WHO as a central issue in patient safety [72].

Despite the need for developing healthcare professionals’ and patients’ communication skills, (ongoing) face-to-face training is rather time-consuming and may not be achievable given the overall need for increasing hospital efficiency [73]. Digital communication training offers a solution to this dilemma as it reduces costs and organization resources. Moreover, users can participate in the training according to their own schedules, thus potentially increasing their motivation and the training’s effectiveness, but only if the digital trainings are sufficiently implemented and monitored [74].

Two studies included in a previous review evaluated the effectiveness of training interventions to improve communication [9]. The training package targeting communication skills for doctors was not associated with higher satisfaction with work scores recorded by women, although they reported high satisfaction with training workshops [75]. While Crofts et al. reported that improvements in all their test variables in the three clinical scenarios were statistically significant after the training, this was based on a pre- and post-intervention analysis with no comparison groups [76]. Perceptions of safety and communication significantly improved after training with patient-actors, compared to training using mannequins for postpartum hemorrhage scenarios, but it is unclear why no statistically significant improvements were found. Furthermore, the authors revealed no benefits of additional teamwork training on patient-actor perceptions of care related to safety, communication, and respect [76]. Due to the innovative aspects outlined above, our own evaluation is expected to outperform these previous effects in order to support communication. This study will also provide valuable information on the effectiveness, user-acceptability, and feasibility of the intervention. It addresses the need to investigate new approaches to improve communication, which can relieve health systems from the growing demands caused by challenges with communication around the world and in all areas of medicine and public health.

## Data Availability

The full protocol including data security protocol (in German)  and publication guidelines will be available from the corresponding author on reasonable request. Data sharing is not applicable to this article as no datasets were generated or analyzed so far.

## Abbreviations

BCT: Behavior change techniques
CG: Control group
HAPA: Health Action Process Approach
IG: Intervention group
N/n: Number of study participants
NPWT: Negative-pressure wound therapy
pAEs: Preventable adverse events
RCT: Randomized controlled trial
SACCIA: “Sufficiency”, “Accuracy”, “Clarity”, “Contextualization”, and “Interpersonal Adaptation”
SBAR: “Situation”, “Background”, “Assessment”, and “Recommendation”
WHO: World Health Organization
